### Participants

A total of 110 young adults aged 18 to 25 years will be recruited. The eligibility range was narrowed to 18 to 25 years to improve developmental homogeneity and align the sample with late adolescence and emerging adulthood, a period marked by elevated risk for depression and anxiety [1-4]. The participant eligibility criteria are shown in Textbox 1. Participants will be recruited through advertisements at local universities, vocational colleges, and community health centers.

Participant eligibility criteria.

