### Sample Size Calculation

An a priori power analysis was conducted using G*Power. On the basis of meta-analyses of related VR-based mental health interventions [30,31], a medium effect size (f=0.25) was assumed. To achieve 80% power at an alpha level of .05 for the primary group-by-time comparison, a required sample of 90 participants was indicated. To account for an anticipated attrition rate of 20% to 30%, consistent with rates reported in VR intervention literature, the recruitment target is set at 110 participants. A sensitivity analysis indicates that with 30% attrition (leaving approximately 77 participants), statistical power for the primary comparison would be reduced to approximately 70%, which is acknowledged as a limitation. To minimize attrition, the study will implement flexible scheduling, session reminders, brief mid-study check-ins, and graduated VR exposure in the first session to identify and manage cybersickness early. If observed attrition exceeds 30%, this will be reported transparently and considered in the interpretation of results. This sample size determination was made for the primary clinical outcomes and was not specifically powered for mediation or moderation analyses; those analyses will therefore be treated as exploratory.

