### Randomization and Blinding

A computer-generated random number sequence with variable block sizes will be used to allocate participants in a 1:1:1 ratio. Randomization will be stratified by gender and primary presenting concern (depression vs anxiety) to ensure balanced group allocation on these prognostically important variables. The allocation sequence will be concealed from research staff responsible for recruitment. Because of the nature of the intervention, participants and session facilitators cannot be blinded. Outcome data will be collected primarily through self-report instruments administered through a secure platform, and analyses will be conducted on deidentified group codes until the primary models are finalized.

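### The recruitment target of 110 retains the required 90 only up to about 18% attrition, so it does not cover the 20% to 30% it is said to cover

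*Protocol article*

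**What the plan says.** All the relevant figures stand in the Sample Size Calculation section of the protocol article. The assumed effect is stated as "a medium effect size (f=0.25) was assumed". The aim is given as "To achieve 80% power at an alpha level of .05 for the primary group-by-time comparison", for which "a required sample of 90 participants was indicated". The next sentence moves from 90 to the recruitment target. It opens "To account for an anticipated attrition rate of 20% to 30" per cent and concludes that "the recruitment target is set at 110 participants". A sensitivity statement follows: "with 30% attrition (leaving approximately 77 participants), statistical power for the primary comparison would be reduced to approximately 70" per cent, and the section acknowledges this as a limitation.

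The Participants section repeats the target ("A total of 110 young adults aged 18 to 25 years will be recruited"), as does the Methods part of the Abstract. In the Discussion, the sixth limitation says that the study is powered for the primary clinical outcomes, though not for mediation or moderation. That statement carries no condition on attrition, and the listed limitations do not mention the reduced power at 30%.

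**The concern.** A target that accounts for a range of attrition should leave the required number at every rate in that range, or at least at its lower end. Here the required number, the range and the target are all stated, so the claim can be checked without any outside figure, and it fails at both ends. It also conflicts with the sentence that follows: 30% lies inside the range the target is said to cover, yet at 30% the section itself reports 77 participants and a loss of about 10 points of power.

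What is at stake is how the result is read. A reader who takes the target sentence and the Discussion at face value will judge a null result against 80% power. On the plan's own attrition assumption, expected power lies between just under 80% and about 70%.

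**Working it through.** **Inputs, all from Sample Size Calculation unless noted**
- Required sample N = 90, for 80% power at alpha .05
- Anticipated attrition d = 20% to 30%
- Recruitment target R = 110
- Stated result at 30%: about 77 participants, about 70% power
- Three equal arms (Randomization and Blinding: "allocate participants in a 1:1:1 ratio")

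**Step 1. The plan's own sensitivity figure.** Retained = R × (1 − d) = 110 × 0.70 = 77. This reproduces, and it shows that the plan counts retained participants in this way.

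**Step 2. The same formula across the range, with the recruits needed, N / (1 − d), rounded up.**

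| Attrition | Retained from 110 | Short of 90 | Recruits needed to retain 90 | 110 falls short by |
|---|---|---|---|---|
| 20% | 110 × 0.80 = 88 | 2 | 90 / 0.80 = 112.5, so 113 | 3 |
| 25% | 110 × 0.75 = 82.5 | 7.5 | 90 / 0.75 = 120 | 10 |
| 30% | 110 × 0.70 = 77 | 13 | 90 / 0.70 = 128.6, so 129 | 19 |

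**Step 3. The attrition that 110 can absorb.** 1 − 90/110 = 0.182, or about 18%. This is below the bottom of the stated range.

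**Step 4. Where 110 might come from.** The article does not say. Multiplying by (1 + d) instead of dividing by (1 − d) gives 90 × 1.20 = 108 at 20%, which is close to 110, and 90 × 1.30 = 117 at 30%. That is only a possible explanation, and nothing below depends on it.

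**Step 5. Power across the range.** Take the plan's premise that 90 gives exactly 80%. Let the noncentrality of an F test be proportional to the number retained, solve for the constant that gives 80% at 90, and recompute. With 1, 2 or 4 numerator degrees of freedom, and N − 3 or 2(N − 3) in the denominator, power is:
- at 88: 78.9% to 79.1%
- at 82.5: 75.7% to 76.5%
- at 77: 72.2% to 73.5%

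The plan's own figure at 77, about 70%, is slightly lower than this rescaling and so does not flatter the design.

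**Step 6. The two arms of the primary comparison.** That comparison is experimental against active control, two of three equal arms. At 90 it would have 60 participants. At 88 it has 88 × 2/3, about 59, and at 77 it has 77 × 2/3, about 51.

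**A limit of this check.** The 90 is taken as given. The article does not state the number of groups, the number of measurements or the correlation used in G*Power, and different options at f = 0.25 give very different totals. For three groups and three time points, the default interaction test with correlation 0.5 gives 35, and two alternative effect-size conventions give 98 and 101. A three-group one-way test gives 158. None of this alters steps 1 to 3.

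**The case against.** The case against rests on size, disclosure and consequence, and much of it stands.

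- **The lower end is close to rounding.** At 20% the target is 3 below 113 (2.7%), and the loss is about 1 point of power. That the target fails throughout the range is true, but at 20% the failure has no practical weight.
- **The worst case is already printed.** The sentence after the target gives 77 participants and about 70% power. A reader might infer that the shortfall is concealed. The document does not support that: the lower bound on power is in plain view, and only the rest of the range is left unstated.
- **Participants who leave are not all lost to the analysis.** Data Collection and Analysis includes all randomized participants with available data, and Data Management specifies mixed models fitted by maximum likelihood. Someone who leaves between week 6 and week 10 still contributes to the week 6 contrast. Retained counts are therefore a cautious basis for power, at least at week 6. Against this, the section's own sensitivity case counts retained participants, and someone with baseline data only adds little.
- **Attrition may be lower than anticipated.** The section lists retention measures and does not say whether 20% to 30% is before or after their effect.

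A reader might go further and infer that 80% power can never apply to this trial. The document does not support that either. It attaches 80% to 90 participants, 110 retains 90 if attrition is 18% or less, and about 79% at the lower end is 80% for practical purposes.

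What the objections do not remove is the sentence itself. It says that 110 allows for a range which, on the same paragraph's figures, it does not.

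**Conclusion.** The statement is wrong as written. On the plan's own figures, 110 covers attrition up to about 18%, not 20% to 30%. The shortfall runs from 2 participants (about 79% power) at 20% to 13 participants (about 70% by the plan's figure, 72% to 73.5% by rescaling) at 30%. It is trivial at the lower end and material toward the upper end, where it is disclosed but contradicted by the sentence before it.

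The counts need only the stated 90, 110 and attrition range. The power figures also assume that 90 gives exactly 80%, and that someone who drops out contributes nothing. The second assumption is the plan's own way of counting and is somewhat cautious.

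The design, the analysis and the type I error rate are unaffected. This should be fixed, as a correction to a stated property of the sample size. It is not a reason to change or delay the trial.

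**What to change.** In Sample Size Calculation, replace the sentence that links attrition to the target with wording such as:

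> 110 participants will be recruited, which retains the required 90 at attrition up to about 18%; at the anticipated 20% to 30%, 88 to 77 participants are expected, with power of about 79% falling to about 70% on the same assumptions.

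The 79% comes from the rescaling above and the 70% from the plan, so the authors should confirm both from their own G*Power settings before printing them together.

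In the Discussion, qualify the sixth limitation in the same way: the study reaches its planned power for the primary clinical outcomes only if attrition stays at or below about 18%, with expected power below 80% across the anticipated range.

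The cost is two edited sentences and a slightly less favourable stated power. Recruitment need not change. If the sponsor would rather keep the claim that the target covers the range, the target would have to rise to 113 for 20% attrition and to 129 for 30%. As of April 2026 no participants had been enrolled, so that option was still open.

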### Interventions

#### Experimental Group: VR Social Musical Exergame

Participants in this arm will engage in the VR intervention twice a week for 45 minutes over 6 weeks. Prior to the first intervention session, all participants in VR conditions (experimental group and active control group) will complete a 15-minute familiarization session using a neutral, nontherapeutic VR environment to reduce initial novelty effects and identify individuals who may experience significant cybersickness. Waitlist control participants will receive a brief (5-minute) VR demonstration to partially equalize technology exposure. The experimental condition is conceptualized as a bundled social VR musical exergame designed to support autonomy, competence, and relatedness simultaneously.

#### Autonomy

Participants are afforded choice through customization of their avatars and selection from a curated library of music genres and movement patterns.

#### Competence

The exergame requires participants to hit virtual targets in synchrony with musical beats. Real-time visual and auditory feedback, performance scores, and adaptive challenge levels are intended to support mastery and perceived capability [33,34].

#### Relatedness and Social Layer

Participants interact in multiuser virtual rooms for collaborative and competitive team tasks, with real-time voice chat enabled to support communication and social connection. Each session will include a minimum of 10 minutes of structured collaborative or competitive team tasks and at least 5 minutes of open voice chat interaction with coparticipants. The social manipulation therefore comprises multiple elements, including peer communication, collaboration, and structured social comparison. Accordingly, the trial tests the added value of this bundled social layer rather than the isolated effect of any single social feature.

#### Active Control Group: VR Solo Musical Exergame

This group will engage in a VR exergame with the same frequency, duration, exercise intensity, game content, and music design as the experimental group. However, all social features will be disabled. This condition is designed to preserve autonomy and competence support while removing the bundled social layer, and it serves as the primary comparator for testing the unique contribution of social interaction.

#### Waitlist Control Group

Participants in this group will receive a standardized digital handbook on mental health. They will be instructed to maintain their usual activities for the 6-week study period. To address ethical considerations, this group will be offered access to the VR intervention after the trial. Comparisons with this group are intended as secondary estimates of effects relative to minimal guidance rather than as the primary test of the social mechanism.

### Outcomes

#### Primary Outcomes

The primary outcome will be the change in symptom severity for depression and anxiety.

#### Depression Symptoms

Depression symptoms will be assessed using the Beck Depression Inventory-II (BDI-II), a 21-item self-report questionnaire with established reliability and validity [35]. The validated Chinese version of the BDI-II will be used in this study [36].

#### Anxiety Symptoms

Anxiety symptoms will be assessed using the Beck Anxiety Inventory (BAI), a 21-item self-report questionnaire with demonstrated reliability and validity [37]. The validated Chinese version of the BAI will be used [38].

#### Secondary and Process Outcomes

##### Basic Psychological Need Satisfaction

Basic psychological need satisfaction will be assessed using the Basic Psychological Need Satisfaction Scale, a 21-item measure with evidence supporting its 3-factor structure and use in relevant populations [39,40]. The validated Chinese version will be used, which has demonstrated adequate psychometric properties in Chinese young adult samples [40].

##### Loneliness

Loneliness will be assessed using the University of California, Los Angeles Loneliness Scale, a 20-item instrument with documented psychometric support in adolescent and young adult samples [41]. The Chinese version of the scale, which has been validated in Chinese adolescent populations, will be used [41].

##### Sense of Presence

Sense of presence will be assessed using the Igroup Presence Questionnaire, a 14-item scale for measuring presence in virtual environments [42,43]. A Chinese version of the Igroup Presence Questionnaire will be used, adapted following standard translation and back-translation procedures [44].

##### Cardiorespiratory Fitness

Cardiorespiratory fitness will be estimated using the Young Men’s Christian Association 3-minute step test, a practical field-based measure with established validity [45,46]. This outcome is treated as a secondary health-related outcome rather than as a primary mechanistic SDT variable.

##### Music-Movement Synchronization

Music-movement synchronization is an objective behavioral metric captured by the VR software, reflecting the accuracy and timing of participants’ physical movements relative to musical beats. Within the SDT framework, this variable is treated as an exploratory behavioral indicator that may reflect task engagement and perceived competence. It is not a primary or confirmatory outcome; any associations with other variables will be interpreted as hypothesis generating.

All self-report and fitness measures will be collected at T0, T1, and T2. In-VR behavioral data will be captured continuously during the intervention period.

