#### Secondary Objectives

The secondary objectives of this study are as follows:

To explore whether changes in basic psychological need satisfaction are associated with changes in depression and anxiety symptoms. These analyses are specified as exploratory and hypothesis generating rather than as definitive tests of temporal mediation.To explore whether in-game performance (ie, music-movement synchronization) moderates competence satisfaction and mental health outcomes as an exploratory secondary analysis.To assess the intervention’s effects on loneliness, sense of presence, and cardiorespiratory fitness.

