### Participant Timeline

Following screening and informed consent, eligible participants will complete baseline assessment (T0), undergo randomization, receive the 6-week intervention or waitlist condition, complete the postintervention assessment at week 6 (T1), and complete the follow-up assessment at week 10 (T2; Table 1).

**Table 1 table1:** Schedule of enrollment, interventions, and assessments.

Time point	Enrollment	Allocation	T0^a^	T1^b^	T2^c^
Eligibility screen	✓				
Informed consent	✓				
Randomization		✓			
Intervention			✓		

^a^T0=baseline: week 0.

^b^T1=posttest: week 6.

^c^T2=follow-up: week 10.

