### Data Management

All data will be entered into a secure electronic database with verification procedures. Identifiable information will be stored separately from outcome data on encrypted institutional servers, accessible only to authorized members of the research team.

For the primary outcomes, linear mixed-effects models will be used to examine group, time, and group×time effects on BDI-II and BAI scores. Separate models will be fitted for depression and anxiety outcomes, with participant-level random intercepts to account for repeated measures over time. Gender and primary presenting concern (the stratification variables) will be included as covariates, and baseline symptom severity will be considered in model specification as appropriate. The primary planned contrasts will compare the experimental group with the active control group at T1 and T2; comparisons involving the waitlist control group will be secondary and should be interpreted with caution, given the expectancy and novelty confounds inherent in waitlist comparisons. Post hoc pairwise comparisons will be adjusted for multiple testing using a Holm procedure. Secondary outcomes will be analyzed using analogous mixed-model approaches. Cybersickness (SSQ scores) will be examined as a potential covariate in sensitivity analyses to assess whether differential simulator sickness across groups confounds the primary results. Missing data assumptions will be examined, with maximum likelihood estimation in mixed models as the primary approach and multiple imputation and per-protocol analyses used as sensitivity analyses where appropriate. Exploratory analyses will examine whether changes in Basic Psychological Need Satisfaction Scale scores are associated with changes in BDI-II and BAI scores and whether music-movement synchronization moderates selected outcomes; these analyses will be interpreted as hypothesis generating rather than confirmatory causal tests.

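### Sense of presence is scheduled at a baseline before any trial VR and, on a fair reading, in the waitlist arm, so its change-from-baseline, group×time and waitlist results cannot be interpreted; social versus solo at week 6 still can

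*Protocol article*

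**What the plan says.** Presence is a named secondary outcome. The last aim under Secondary Objectives is "To assess the intervention’s effects on loneliness, sense of presence, and cardiorespiratory fitness". Under Sense of Presence, the instrument is the Igroup Presence Questionnaire, described as "a 14-item scale for measuring presence in virtual environments".

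The schedule is one sentence at the end of the Outcomes section, under Music-Movement Synchronization: "All self-report and fitness measures will be collected at T0, T1, and T2". It makes no exception by instrument or by arm.

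The analysis is under Data Management. For the primary outcomes, "linear mixed-effects models will be used to examine group, time, and group×time effects on BDI-II and BAI scores". For the rest, "Secondary outcomes will be analyzed using analogous mixed-model approaches". Presence is not singled out.

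Three statements fix when VR is experienced:

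- Participant Timeline: "eligible participants will complete baseline assessment (T0), undergo randomization, receive the 6-week intervention or waitlist condition".
- Interventions, experimental group: participants in both VR arms "will complete a 15-minute familiarization session using a neutral, nontherapeutic VR environment" before their first session.
- The same paragraph: "Waitlist control participants will receive a brief (5-minute) VR demonstration to partially equalize technology exposure". When this happens is not stated. The Waitlist Control Group section otherwise provides a digital handbook and usual activities, with access to the VR intervention once the trial is over.

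**The concern.** A presence score needs a virtual environment to refer to. A schedule that suits the depression, anxiety, loneliness and need-satisfaction scales does not suit one whose subject is the VR experience itself. Read together, the schedule and the analysis sentence ask people to rate presence before the trial has shown them any VR. They also ask an arm with almost no VR to rate it on the same footing as arms with twelve scheduled sessions (twice weekly for 6 weeks).

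A named secondary objective is at stake. A rise in presence from T0 in the VR arms, or a gap between those arms and waitlist, would follow from who had been placed in VR. It could still be reported as an effect of the intervention on presence.

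**Working it through.** The article gives no figure for presence, so there is none to reproduce. The check crosses arms and visits with the VR exposure that the article describes.

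**Step 1: order of events.** T0 comes before randomization (Participant Timeline). The 15-minute familiarization is given to the two VR arms, so it depends on allocation and must follow T0. Significant VR motion sickness is an exclusion criterion, but no VR test at screening or T0 is described.

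**Step 2: the cells.** 3 arms × 3 visits = 9 cells.

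| Arm | T0 (week 0) | T1 (week 6) | T2 (week 10) |
|---|---|---|---|
| Experimental (social) | no trial VR yet | 6 weeks of VR | last scheduled VR about 4 weeks earlier |
| Active control (solo) | no trial VR yet | 6 weeks of VR | last scheduled VR about 4 weeks earlier |
| Waitlist | no trial VR yet | at most a 5-minute demonstration | at most a 5-minute demonstration |

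The count is:

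- No trial VR to rate: 3 cells (T0).
- Minimal, non-comparable exposure: 2 cells (waitlist at T1 and T2).
- VR-exposed arms: 9 − 3 − 2 = 4 cells. Two are at T1. Two are at T2, where the interval is 10 − 6 = 4 weeks if no VR is used in between.

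**Step 3: what each estimate uses.** Write E, A and W for mean presence in the experimental, active control and waitlist arms, with the visit number attached.

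- *Change from T0*, for example E1 − E0, subtracts a score with no trial VR behind it. It is not a change in presence.
- *VR versus waitlist*, for example E1 − W1, compares six weeks of sessions with at most five minutes. The difference reflects exposure.
- *The group×time test* across three arms and three visits has (3 − 1) × (3 − 1) = 4 degrees of freedom. Two of them involve waitlist, and all are measured against T0.
- *Social versus solo in change*, (E1 − E0) − (A1 − A0) = (E1 − A1) − (E0 − A0). Because T0 precedes randomization, E0 − A0 has expectation zero. This contrast therefore targets the same quantity as E1 − A1, and the T0 scores supply no change in presence.
- *Social versus solo at T1*, E1 − A1, uses two cells with comparable exposure and needs neither T0 nor waitlist. About 110 × 2/3 ≈ 73 randomized participants contribute, before attrition.

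**Step 4: a comparison within the article.** Under Safety Monitoring and Adverse Events, the other VR-specific questionnaire, for simulator sickness, is tied to exposure: it is completed when each VR session ends. Presence is not tied to exposure.

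**The case against.** The strongest counter-argument is that little depends on this. The primary planned comparison is experimental versus active control, and that contrast on presence is sound at T1. Waitlist comparisons are already labelled secondary and to be read with caution. This stands. A reader might infer that the whole presence result is meaningless, and the documents do not support that.

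Four further points limit how far the criticism reaches:

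- *Presence is not strictly undefined in the waitlist arm.* The demonstration gives those participants something to rate. It is a minimal experience of unstated timing, so their scores are non-comparable rather than impossible.
- *Collection in all three arms is inferred.* The schedule sentence does not mention arms, and analogous models need not be identical ones. Unrestricted wording is nevertheless most naturally read as covering every arm. Table 1, as available here, has no rows for instruments, so an exception there cannot be ruled out.
- *Nothing in the article sets a recall window.* A reader might conclude that T2 presence scores are invalid. The article says only that the scale concerns virtual environments, so that conclusion would need outside knowledge of the instrument.
- *Outcome-specific models may be set out in an analysis plan that is not shown.* That would excuse silence, but the article is not silent. It fixes the visits for all self-report measures, and T0 is one of them.

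The cautions attached to waitlist comparisons concern expectancy and novelty. They do not address the lack of a comparable VR experience to rate, and they do not touch T0.

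**Conclusion.** The point holds in limited form. Under the schedule as written, 3 of 9 cells have no trial VR experience to rate and 2 more have only a minimal, non-comparable one. Change from T0, group×time and VR-versus-waitlist results for presence are therefore not interpretable. Experimental versus active control at T1 is valid and answers the question that the trial is built around. BDI-II, BAI and the sample size are unaffected. This is a defect in one secondary outcome, worth correcting before enrolment; the article reports that nobody had been enrolled as of April 2026.

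The conclusion rests on three assumptions: no VR is used at screening or T0; the schedule sentence applies to all arms; and waitlist access to the VR intervention comes after T2. If access instead began between T1 and T2, the waitlist T2 cell would change, but the T0 cells and waitlist T1 would not.

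**What to change.** In the Outcomes section, exempt presence from T0 and from the waitlist arm, and state which VR experience participants are to rate. In Data Management, exempt presence from the models carried over from the primary outcomes. Analyse it as experimental versus active control after exposure, at T1 and ideally at the last VR session, with no T0 value and no group×time term. The stratification variables can stay as covariates. If T2 presence is kept, label it as recall of VR about 4 weeks earlier (assuming no VR use between T1 and T2) and report it descriptively.

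The cost is schedule and analysis wording, and the loss of a waitlist estimate for presence, which would not have been interpretable. Fewer questionnaires would be administered.
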